### Instructions for using Size Estimation Field Staff Contact Log

- 1. Date:** Write the date of distribution activity.
- 2. Distribution Site:** Write the site in which the distribution activity is taking place.
- 3. Time:** Write the time of distribution activity.
- 4. Age:** If the person is under 15 years old, do not give object or collect any other information.
- 5. Living or working in Cabinda Province:** Ask question: *Do you live or work in Cabinda province?* If answer is no, do not give object or collect any other information.
- 6. Is a female sex worker:** Ask question: *In the past 12 months, have you had received money for sex?* If answer is no, do not give object or collect any other information.
- 7. Have already received [object]:** Ask question: *Have you received a [object] by a field staff member in the past two weeks?*
- 8. Accepted [object]:** Explain that these objects are being distributed for a survey and that the only participation needed from him in this survey is to accept the object and that no other questions will be asked. If the person accepts the object, ask him to keep the object because in about two weeks to four months, someone might ask them again if they have received this object.

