### ***RDS Population Size Procedures***

We will use the unique object multiplier method to obtain a population size estimate of female sex workers in the province of Cabinda. The multiplier method is the most commonly used population size estimation method, in part because it is relatively straightforward and utilizes simple calculations. The unique object multiplier method involves the distribution of a set number of unique objects, such as key chains, to members of the target population. Unique objects will be distributed widely at specific locations where female sex workers congregate (i.e. bars, brothels, hotels, etc.). The goal is to distribute as many unique objects as possible, but no less than the agreed upon study sample size.

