### *Implementation*

NGOs and other organizations will be asked to distribute a specified number of unique objects to female sex workers for a period of two weeks. Each person will receive only one object and will be asked to keep the object because they may be asked about it by another field staff in the near future. Field staff will determine whether the participant has previously received a unique object to avoid double counting. No personal identifying information will be collected.

To estimate population proportions, persons enrolled in survey will be asked if they had received the unique object and be asked to show or describe the object to the interviewer. Those who are in possession of the object or can recall it in sufficient detail will be counted as the proportion who received the unique object. Calculations are then made to estimate the population size.

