**The formula for estimating the population size using a multiplier is**

$$N = \frac{(n_1 \times n_2)}{m}$$

where N is the estimate of total population size; n1 is the number of individuals receiving unique objects; n2 is the number of individuals participating in the RDS; m is the number in both populations (i.e. the number of MSM who received unique objects and participated in the RDS)

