## **Assumptions**

Members of the sex worker, MSM or transgender population must have a chance of being included in both sources of data. Data from both sources will be evaluated for any potential barriers to inclusion of members of the target population. Where this assumption is violated, this will be clearly documented and reported, and other sources of data will be considered.

The multiplier method requires clear and consistent population definitions, time reference periods, and catchment areas between the different data sources. During preparation for implementation of multiplier activities and collection of unique object and survey data, these issues will be carefully considered, and investigators will ensure that definitions across data sources will be coordinated.

**Objective 8: To provide data to inform and guide future behavioral surveys and prevention strategies targeting sex workers, MSM or transgender women in Angola.**

Responses collected at a roundtable meeting with key stakeholders held at the end of data collection will be analyzed. We will invite all USG agencies, local NGOs, and key government officials to discuss how survey results can assist ongoing and future behavioral activities targeting sex workers, MSM and transgender women and how these results can advance priorities outlined in the Country Operating Plan (COP) and Angola's National Strategic Plan (NSP). Priorities for Local AIDS Control Efforts (PLACE) studies in identifying high transmission HIV/AIDS areas to improve HIV prevention program delivery. Combined data from objectives A, B and C will be used to guide the design of new prevention messages targeting sex workers, MSM and transgender women. All results will be shared with NGOs and other agencies working directly with sex workers, MSM and transgender women in Angola.

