| 3. What was the main reason given for refusing to accept a coupon?

(Do not read. Ask for each individual who refused to accept the coupon)

Check all that apply. |  1. Too busy
 2. Already had a coupon
 3. Already participated in survey
 4. Younger than 18
 6. Not resident of _____
 7. Fear of being identified as _____
 8. Site is too far away                         |  1. Too busy
 2. Already had a coupon
 3. Already participated in survey
 4. Younger than 18
 6. Not resident of _____
 7. Fear of being identified as _____
 8. Site is too far away                         |  1. Too busy
 2. Already had a coupon
 3. Already participated in survey
 4. Younger than 18
 6. Not resident of _____
 7. Fear of being identified as _____
 8. Site is too far away                         |  1. Too busy
 2. Already had a coupon
 3. Already participated in survey
 4. Younger than 18
 6. Not resident of _____
 7. Fear of being identified as _____
 8. Site is too far away                         |

|  |                                                                                                                                                        |                                                                                                                                                        |                                                                                                                                                        |                                                                                                                                                        |

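### The object-distribution script wrongly tells recipients that their part in the survey is finished, which risks making the two sources of the Cabinda size estimate dependent

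*Protocol*

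**What the plan says.** The Cabinda size estimate combines two sources (Protocol VI.F, RDS Population Size Procedures). Field staff first hand out unique objects for two weeks. The RDS survey follows, and its participants are asked about the object.

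- **Script.** Appendix 13, instructions, item 8: staff explain that the objects are for a survey, that "the only participation needed from him in this survey is to accept the object and that no other questions will be asked".
- **Next sentence of item 8.** The recipient is asked to keep the object because "in about two weeks to four months, someone might ask them again if they have received this object".
- **Body text.** VI.F, Implementation, also announces later contact: recipients are to keep the object because "they may be asked about it by another field staff in the near future". It does not say that their participation is complete.
- **What happens later.** VI.F, Implementation: "persons enrolled in survey will be asked if they had received the unique object", and they must show or describe it. VI.F, Data Sources, lists seven object questions for the RDS interview.
- **Estimator.** VIII.C gives N = n1 × n2 / m, where "n1 is the number of individuals receiving unique objects", n2 is the number taking part in the RDS and m is the number in both.
- **Assumption.** VIII.C, Assumptions: "Members of the sex worker, MSM or transgender population must have a chance of being included in both sources of data". The section adds that the data will be examined for barriers to inclusion and that violations will be documented and reported.

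**The concern.** The multiplier reads the share of RDS participants holding an object as the share of all female sex workers holding one. That works only if holding an object does not change the chance of joining the RDS.

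Item 8 is said only to women offered an object. Taken at its word, it tells them that they have already done what the survey needs. A woman who believes that has a reason to decline a coupon that a non-recipient does not have. If some decline, m is too small, N is too large, and programme coverage calculated on N is too low. Women reached at the distribution sites (bars, brothels, hotels) would also be under-represented in the RDS prevalence and behaviour estimates. RDS weights adjust for network size and recruitment pattern, not for a staff message given to one group.

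The planned review of barriers would have difficulty seeing this. The RDS non-response form (Appendix 6) does not record whether a person who refused a coupon held an object.

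**Working it through.** **1. Is the statement true under the plan?** No. Item 8 says no other questions will be asked in this survey. VI.F puts the object questions into the RDS interview, and the estimator cannot be calculated without the answers. Item 8's second sentence also announces a further question. The conflict is on the face of the document and needs no assumption.

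**2. What would follow if it changed participation?** The Protocol states no Cabinda population size, expected m or precision target, so there is no planned figure to reproduce.

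Inputs:
- n2 = 400: approximate Cabinda RDS sample (VI.E, Sample Size).
- n1 = 400: the floor in VI.F, which sets distribution at "no less than the agreed upon study sample size".
- True N = 1000 or 2000: assumed.
- f, the rate at which recipients join the RDS relative to non-recipients: assumed.

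When the RDS is a small share of the population, the expected share of participants with an object is

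m/n2 = f·n1 / (f·n1 + N − n1).

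Putting this into N = n1 × n2 / m gives

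estimate = n1 + (N − n1)/f.

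Dividing by N, with coverage p = n1/N, gives the error factor p + (1 − p)/f.

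| f | N = 1000 (p = 0.4) | N = 2000 (p = 0.2) |
|---|---|---|
| 1.25 | 400 + 600/1.25 = 880 (−12%) | 400 + 1600/1.25 = 1680 (−16%) |
| 1 | 1000 (0%) | 2000 (0%) |
| 0.9 | 400 + 600/0.9 = 1067 (+7%) | 400 + 1600/0.9 = 2178 (+9%) |
| 0.8 | 400 + 600/0.8 = 1150 (+15%) | 400 + 1600/0.8 = 2400 (+20%) |
| 0.5 | 400 + 600/0.5 = 1600 (+60%) | 400 + 1600/0.5 = 3600 (+80%) |

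At N = 2000, f = 0.8 lowers the expected overlap from 80 to 66.7.

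**3. Limit of the formula.** If the RDS takes 400 of 1000 women without replacement, it is not a small share. Simulation then gives about +5%, +12% and +44% for f = 0.9, 0.8 and 0.5, so the N = 1000 column somewhat overstates the error.

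**4. Effect of object coverage.** VI.F, Sample Size, aims to saturate the population with objects.
- p = 0.9, f = 0.8: 0.9 + 0.1/0.8 = 1.025 (+2.5%).
- p = 0.9, f = 0.5: 0.9 + 0.1/0.5 = 1.10 (+10%).
- p = 1: factor 1 for any f, so no bias.

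**5. Scale.** At N = 2000 the simple binomial relative standard error is √((1 − 0.2)/(0.2 × 400)) = 0.10, a 95% margin of about ±20%. A bias at f = 0.8 would be about as large, and recruiting more RDS participants would not reduce it.

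**The case against.** The strongest reply is that nothing in the Protocol shows recipients would stay away. Item 8 can be read as covering only the distribution encounter, and its next sentence announces later contact. Entry to the RDS is separate: a peer hands over a coupon that states neither the target population nor the exact purpose, the participant receives a gift worth 900 Kwanzas, and the recruiter is rewarded as well (VI.D, Coupon and Incentives). Recipients have also met staff and been given something, so they may join more readily, in which case N is understated. At the saturation the plan aims for, the error largely disappears.

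Most of this stands. A reader might infer that the script does discourage recipients and that the Cabinda size is therefore overstated. The Protocol does not support that: it gives no participation by object status, so both the size and the sign of any effect are unknown. Two further readings also go too far:

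- The Assumptions text asks only for a chance of inclusion in both sources, and the script does not remove that chance. The difficulty is dependence between the sources, not exclusion from one.
- The Appendix 6 refusal option "3. Already participated in survey" is an ordinary one for women already enrolled, and nothing ties it to object recipients. It shows only that such refusals would not be distinguishable on the form.

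The reply does not rescue the wording. The text says in this survey, not today. The sentence about later contact announces a check on the object; it does not say that recipients may still take part in an interview. Saturation is an aim: VI.F also ties the number of objects to logistics, staffing and the contacts expected in one to two weeks.

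**Conclusion.** Item 8 makes a statement that the plan itself contradicts, and makes it only to women offered an object, whose later participation the estimator depends on. That is an avoidable risk of dependence between the two sources, not a demonstrated bias.

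Under an assumed f of 0.8 and the minimum of 400 objects, the estimate would be about 15% too high at N = 1000 (about 12% allowing for the large RDS share) and 20% too high at N = 2000. The +60% and +80% results need recipients to join at half the rate of other women, which nothing in the Protocol suggests. Any under-representation of venue-based women in the RDS estimates rests on the same unproven condition, f below 1.

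The wording should be changed because the change is nearly free and cannot be made once the objects are out.

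**What to change.** In Appendix 13, item 8, delete the statement that "the only participation needed from him in this survey is to accept the object and that no other questions will be asked". Replace it with neutral wording that makes three points:

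- no more questions will be asked today;
- accepting the object neither counts as taking part in any later survey nor prevents it;
- she should keep the object because she may be asked about it later.

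The replacement should not promote the RDS or mention invitations from peers. Saying that to recipients alone could push f above 1 and create dependence in the other direction.

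The cost is one edited instruction and a few minutes of staff training before distribution, with no extra staff, visits or participants.
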